#### Secondary Outcomes

Several secondary outcomes will be assessed:

Internal UV-dose will be determined by measuring the SC levels of UCA isomers and immunological markers measured in the intervention and control groups at T = 0, T = 6 weeks, and T = 12 weeks.Levels of external UV-exposure in construction workers, measured using Scienterra UV-dosimeters at T = 0, T = 6 weeks, T = 12 weeks.The prevalence of NMSC including AK in construction workers as assessed at T = 12 weeks by a skin check.The number of reported episodes of sunburn during the study period as obtained from the closing questionnaire at T = 12 weeks.

#### Process Outcomes

Pattern of sunscreen use derived from data generated by the electronic monitoring system of the sunscreen dispensers, in the intervention groups only. This will include frequency (averaged for the number of workers), time of use, association with UV-exposure and job task, averaged per person and day.Pattern of sunscreen use in relation to the time after placing a poster with feedback concerning UV-index and sunscreen consumption (in the intervention groups only, derived from electronic monitoring).Satisfaction with the intervention by the construction workers and employers as assessed by the closing questionnaire. The questions concern satisfaction with the sunscreen (ease of use, ability to perform job task etc.), and satisfaction with the placement of the dispensers (in the intervention groups only).Changes in UV-protective behavior regarding sunscreen use. This will be assessed from the questionnaires collected at T = 0 and T = 12 weeks from the questions related to attitude and motivation to use sunscreen.Identification of possible barriers to using sunscreens will be assessed from the questionnaires collected at T = 0 and T = 12 weeks. The questions address barriers such as difficulty to implement in the work shift, disturbance of work tasks or negative comments from colleagues when applying sunscreen.Knowledge about UV-exposure and UV-protection that will be assessed from the questionnaires at T = 0 and T = 12 weeks. Questions include awareness that applying of sunscreen is important even on cloudy days or on already tanned skin.

### Power Calculation

The study is planned to include 200 participants. The sample size is based on the expectation regarding the change in sunscreen usage. There is no available data on sunscreen use in outdoor workers in the Netherlands, or the barriers for sunscreen use. Therefore, we based our calculations of the sample size on a Canadian study reporting that 25% of the outdoor workers used sunscreen regularly (47). We assumed that 25% of the outdoor workers in the control groups will use sunscreen, and that in the intervention groups we expect this percentage will increase up to 50%. To calculate the sample size, nQuery Advisor software (Statistical Solutions Ltd, Boston, MA, U.S.A.) was used (proportion, two groups, two-sided test). A sample size of 58 workers per group will have 80% power to detect a difference in proportion that equals at least 0.05 significance level. Taking into account possible drop-outs, 100 outdoor workers per group will be recruited.

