## Methods/Design

### Design and Setting

This is a non-randomized controlled intervention study in construction workers. The duration is 12 weeks, from May to July. The measurements will consist of questionnaires, clinical and biochemical assessments, personal UV-dosimetry, and continuous electronic sunscreen consumption records. When reporting the results of this study we will adhere to the Transparent Reporting of Evaluations with Non-randomized Designs (TREND) statement (24).

A nationwide construction company in the Netherlands will appoint four comparable construction sites suitable for the study. Two sites will serve as the intervention groups and the other two construction sites will serve as the control groups. To minimize potential bias induced by non-randomization, the control groups will be matched to the intervention groups regarding worksites and job tasks, geographical location of the worksites, and time-frame. To avoid contamination bias, the whole construction site will be assigned en masse to the intervention group and there will be no rotation of workers between the four workplaces.

A process evaluation of the intervention will take place in the closing questionnaire to support a future implementation process.

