### Statistical Methods and Data Analysis

There will be no replacement of any individual subjects who withdraw. However, the characteristics (e.g., job task, age) and number of withdrawals will be monitored.

The characteristics of the construction workers (e.g., age) and job tasks will be presented by using descriptive statistics. We will use the mean and standard deviation to describe normally distributed continuous variables and the median and interquartile range to describe non-normally distributed continuous variables. For the self-reported sunscreen usage data (primary outcome), counts and percentages to present categorical variables will be used. The self-reported sunscreen usage data will be dichotomized and analyzed by Chi-squared statistical test to establish whether sunscreen consumption will differ between the intervention and control groups. Two-sided *p*-values of <0.05 will be considered statistically significant and statistical uncertainty will be expressed using two-sided 95% confidence intervals. For the main study parameter, intention-to-treat analysis will be performed.

For the secondary study parameters we will present the levels of biomarkers and the number of sunburn episodes as quantitative, continuous variables. The biomarker levels at T = 6 weeks and T = 12 weeks will be compared with the baseline levels using paired ANOVA test followed by the correction for multiple testing, dependently on the distribution of data. The presence of NMSC including AK will be presented as counts and percentages.

UV-exposure measured by UV-dosimeters will be presented per job task, and as average of the measurements by all workers who worn the dosimeter in the same period. Data will be presented as average dose per day. Furthermore, the UV-exposure pattern during the work shift will be revealed.

The distribution will be tested by using Shapiro-Wilk normality test.

Before data analysis, a detailed data analysis plan will be available.

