Recently, a randomized control crossover trial in the United Kingdom (48) which aimed to reduce UV-exposure in the summer, found outdoor workers were exposed to relatively high UV levels in the summer. From the measured UV-dose, approximately a two-fold increase in the risk of being diagnosed with NMSC could be expected if the exposure continued their whole life. The intervention was based on increasing awareness by sending daily messages on the smartphone with recommendations for appropriate measures to reduce UV-exposure. However, this intervention failed to reduce exposure to UV (48). Another study in the United Kingdom found a slight (non-significant) change in sun protective behavior in construction workers after showing them an educational video (49). Our study is focused on reducing internal UV-exposure by using sunscreen. To remove possible barriers such as availability, accessibility, and the costs of sunscreen (10, 21, 22), we provide sunscreen dispensers placed at easily accessible places. Furthermore, we will electronically monitor the amount of sunscreen used, and provide regular feedback on sunscreen use by means of posters. In general, monitoring and feedback are widely used as a strategy to induce behavior change and have been shown to be effective when baseline performance is low, and it is provided more than once (50). Also group monitoring is recognized as being more effective than monitoring systems based on tracking individual actions which do not exploit the stimulating effect of group coherence (50). However, a recent systematic review found that there is very low quality evidence that company-oriented safety interventions reduce injuries among construction workers, and action is needed to increase the adherence of construction workers and employees to protection measures (51).

Strong points of this study are the real-time monitoring of sunscreen use, facilitation of sunscreens, feedback on sunscreen use, and the objective assessment of external and internal UV-dose by using, respectively UV-dosimetry and biomarkers of UV-dose. Also, assessment of the prevalence of NMSC including AK in outdoor workers by a physician will provide evidence on the prevalence of occupational skin cancer in construction workers.

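### The stated 80% power with 58 workers per arm holds only if workers are independent, but four whole sites are assigned and neither the power figure nor the planned chi-squared test allows for site

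*Protocol article*

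**What the plan says.** The Power Calculation section sets the control proportion ("We assumed that 25% of the outdoor workers in the control groups will use sunscreen") and a value of 50% for the intervention arm, and names the calculation as "proportion, two groups, two-sided test". The result is: "A sample size of 58 workers per group will have 80% power to detect a difference in proportion". The sentence then ties the difference to the 0.05 significance level and never prints the detectable difference itself. The step to the recruited number has one stated reason: "Taking into account possible drop-outs, 100 outdoor workers per group will be recruited". Here "group" must mean arm, since 2 × 100 gives the planned 200. No drop-out rate, ICC or design effect is given.

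Design and Setting describes four sites, two per arm, matched on worksite, job tasks, location and time-frame. On the unit of assignment it says that "the whole construction site will be assigned en masse to the intervention group". Dispensers and feedback posters are installed per site.

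Statistical Methods and Data Analysis fixes the primary test: self-reported use is dichotomised and compared by a chi-squared test at two-sided 0.05, with no site term. The limitations in the Discussion cover lack of randomisation, information given to controls, recall and dosimeter position, but not clustering.

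**The concern.** A two-proportion sample size counts each worker as a separate piece of information. Here the site is the unit assigned, and everything that distinguishes the arms is delivered to a site as a whole. If workers on a site resemble each other in sunscreen use, 58 workers on two sites carry less information than 58 independent workers.

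Two things are at stake. The stated power may not be attained. And a test that ignores site will declare significance too often when the intervention does nothing, so a positive result could be taken as stronger evidence than it is.

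**Working it through.** **Inputs.** From Power Calculation: p1 = 0.25, p2 = 0.50, two-sided test, 58 per arm for 80% power, 100 per arm recruited. From Statistical Methods: alpha 0.05 two-sided, individual-level chi-squared test. From Design and Setting: 2 sites per arm, so m = 29 workers per site at 58 per arm and m = 50 at 100 per arm (equal site sizes assumed). The ICC is not in the document; 0.01 to 0.05 is an assumption.

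**Step 1: the plan's own figure.** With pooled proportion 0.375:

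- s0 = √(2 × 0.375 × 0.625) = 0.6847
- s1 = √(0.25 × 0.75 + 0.50 × 0.50) = 0.6614
- n = [(1.960 × 0.6847 + 0.842 × 0.6614) / 0.25]² = 57.7, so 58 per arm

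Power at 58 is 80.2%, and at 100 it is 96.0%. The stated number is therefore the independent-workers calculation with nothing added for site.

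**Step 2: a design-effect-adjusted test.** DE = 1 + (m − 1) × ICC, effective n = n / DE, and power = Φ[(0.25 × √(effective n) − 1.960 × s0) / s1]. Example: m = 29, ICC = 0.01 gives DE = 1 + 28 × 0.01 = 1.28, effective n = 58 / 1.28 = 45.3, power 69.7%.

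**Step 3: a site-level t-test.** Four sites and two arms leave 4 − 2 = 2 degrees of freedom. The noncentrality is 0.25 / [s1 × √(DE / n)], with critical value 4.303.

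**Step 4: the planned chi-squared test.** Its critical value stays at the independence value while the true standard error grows by √DE. Rejection probability at 25% versus 50% is Φ[(0.25 × √n − 1.960 × s0) / (s1 × √DE)]. True type I error is 2 × [1 − Φ(1.960 / √DE)].

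| Per site | ICC | DE | Effective n per arm | Adjusted test, power | Site-level test (2 df), power | Chi-squared, rejection rate | Chi-squared, type I error |
|---|---|---|---|---|---|---|---|
| 29 | 0 | 1.00 | 58 | 80% | 37% | 80% | 5% |
| 29 | 0.01 | 1.28 | 45 | 70% | 31% | 77% | 8% |
| 29 | 0.02 | 1.56 | 37 | 61% | 27% | 75% | 12% |
| 29 | 0.05 | 2.40 | 24 | 43% | 20% | 71% | 21% |
| 50 | 0 | 1.00 | 100 | 96% | 53% | 96% | 5% |
| 50 | 0.01 | 1.49 | 67 | 86% | 41% | 92% | 11% |
| 50 | 0.02 | 1.98 | 51 | 74% | 33% | 89% | 16% |
| 50 | 0.05 | 3.45 | 29 | 50% | 22% | 83% | 29% |

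**Step 5: where 80% is kept.** For the adjusted test, the effective n must be at least 58. With 50 per site: ICC ≤ (100/58 − 1)/49 = 0.015. With 40 per site: ICC ≤ (80/58 − 1)/39 = 0.010. With 29 per site: ICC = 0 only.

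With two sites per arm fixed, the n per arm needed is 58 × (1 − ICC) / (1 − 58 × ICC / 2). This is 81 at ICC 0.01 and 136 at 0.02, and has no solution from ICC = 2/58 = 0.0345 upwards. Beyond that point, more workers on the same four sites cannot restore 80%.

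**The case against.** The strongest objection is that the figures in Steps 2 and 3 belong to tests the protocol does not plan. For the chi-squared test it does plan, the rejection rate falls much less, and with 100 per arm it stays above 80% across the assumed range. That stands, and it shifts the main harm from lost power to false positives. It does not rescue the statement: at 58 per arm the rejection rate is below 80% for any positive ICC, and where it is higher the test is no longer run at 0.05.

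A reader might infer, without condition, that the design lacks 80% power. The document does not support that. It recruits 100 per arm, and an adjusted test keeps 80% up to an ICC of about 0.015 if nobody drops out. But the 42 extra workers per arm are allotted to drop-out, so they are a cushion only as far as they are not lost.

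A reader might also take the remark that systems tracking individuals are ones "which do not exploit the stimulating effect of group coherence" as proof that workers on a site will answer alike. It reports cited literature on monitoring, and makes correlation plausible on the intervention sites only. Matching of sites may reduce between-site variation. Nothing in the document fixes an ICC, high or low.

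The promised detailed analysis plan may add a site term. It cannot make the published power figure true, and the article already names the primary test.

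The run-together of difference and significance level is a wording slip, since 25%, 50% and 0.05 can all be found in the text.

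**Conclusion.** The point stands in conditional form. The arithmetic of 58 per arm is right; the independence assumption behind it does not fit a design with two whole sites per arm, and it is not declared. At 58 per arm any positive ICC brings power below 80%, with either the planned or a site-adjusted test. For ICC 0.01 to 0.05, power at a true 5% level is 70% to 43% (29 per site) or 86% to 50% (50 per site) with a design-effect adjustment. With a site-level test on 2 degrees of freedom it is 31% to 20% or 41% to 22%, and at most 53% even at ICC = 0.

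The planned chi-squared test trades this loss for a type I error of about 8% to 21% or 11% to 29%. A falsely positive finding is therefore at least as serious a risk as a misread null one.

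Confidence is high for the direction and moderate for the size, which rests on the assumed ICC, equal site sizes and normal approximations.

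**What to change.** Keep the enrolment of 200 and make three changes.

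1. **Power Calculation.** State the difference (0.25) and the two-sided alpha (0.05) separately. Say that 58 per arm gives 80% only if workers are independent. Tabulate power for ICC 0.01, 0.02 and 0.05 against the evaluable number per site (for example 29, 40 and 50), for a named analysis that accounts for site.
2. **Statistical Methods.** Use that same analysis for the primary outcome in place of the unadjusted chi-squared test, or keep the chi-squared result and label it descriptive. A power table beside an unchanged chi-squared test would describe an analysis the study does not run.
3. **Framing.** Describe the study as estimating the effect, with its confidence interval, rather than as powered at 80%, and add clustering to the limitations.

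The cost is a rewritten paragraph and a changed primary analysis, with no extra participants. The stated power becomes less favourable and the confidence intervals wider. Recruitment had not started at submission, so the change can be made before any data exist.

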### Statistical Methods and Data Analysis

There will be no replacement of any individual subjects who withdraw. However, the characteristics (e.g., job task, age) and number of withdrawals will be monitored.

The characteristics of the construction workers (e.g., age) and job tasks will be presented by using descriptive statistics. We will use the mean and standard deviation to describe normally distributed continuous variables and the median and interquartile range to describe non-normally distributed continuous variables. For the self-reported sunscreen usage data (primary outcome), counts and percentages to present categorical variables will be used. The self-reported sunscreen usage data will be dichotomized and analyzed by Chi-squared statistical test to establish whether sunscreen consumption will differ between the intervention and control groups. Two-sided *p*-values of <0.05 will be considered statistically significant and statistical uncertainty will be expressed using two-sided 95% confidence intervals. For the main study parameter, intention-to-treat analysis will be performed.

For the secondary study parameters we will present the levels of biomarkers and the number of sunburn episodes as quantitative, continuous variables. The biomarker levels at T = 6 weeks and T = 12 weeks will be compared with the baseline levels using paired ANOVA test followed by the correction for multiple testing, dependently on the distribution of data. The presence of NMSC including AK will be presented as counts and percentages.

UV-exposure measured by UV-dosimeters will be presented per job task, and as average of the measurements by all workers who worn the dosimeter in the same period. Data will be presented as average dose per day. Furthermore, the UV-exposure pattern during the work shift will be revealed.

The distribution will be tested by using Shapiro-Wilk normality test.

Before data analysis, a detailed data analysis plan will be available.

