#### Intervention Groups: Sunscreen Dispensers and Feedback Posters

The intervention groups will be provided with electronic sunscreen dispensers (with monitoring system) installed at the construction site at readily accessible strategic places (canteen/offices etc.). The electronic dispenser, equipped with a Wi-Fi transmitter, continuously records each application event, providing information on the timing and frequency of sunscreen use during the work shift. The system provides robust and easy to interpret web-based reports on sunscreen use per dispenser. Data on use pattern (frequency, total consumption, moments of use) and trends will enable structured feedback on sunscreen use to be given to the construction workers to motivate and improve compliance. Feedback on sunscreen use will be provided using posters placed in proximity of the dispensers, and will be replaced with actual data every 2 weeks. To increase the readability and understanding of the information on the posters, visual aids will be used when possible. Recent systematic reviews found that processing a message in a colorful and illustrative format transmits the message more effectively (45, 46). Also, with the increase of foreign nationals in construction, the use of visual means for conveying health and safety messages is widely popular (45).

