### Outcome Measures

#### Primary Outcome

The individual frequency of sunscreen use will be derived from the questionnaires. When asked how often sunscreen is applied on a daily basis in the last month, the answer options are “never, seldom, sometimes, often, always.” Difference in the frequency of sunscreen use between the intervention and control groups will serve as the primary outcome.

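### The primary chi-squared test treats workers as independent although whole sites are assigned, two per arm; with any positive within-site correlation, its p-value is too small and its 95% CI too narrow

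*Protocol article*

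**What the plan says.** Under Design and Setting, the protocol article states "Two sites will serve as the intervention groups and the other two construction sites will serve as the control groups". To limit contamination, "the whole construction site will be assigned en masse to the intervention group". There is no randomization; instead "the control groups will be matched to the intervention groups regarding worksites and job tasks", and also on location and time-frame.

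The intervention is delivered to sites rather than to individuals. Dispensers are shared, and "Feedback on sunscreen use will be provided using posters placed in proximity of the dispensers" (Intervention Groups: Sunscreen Dispensers and Feedback Posters).

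The primary outcome is a between-arm contrast: "Difference in the frequency of sunscreen use between the intervention and control groups will serve as the primary outcome". Statistical Methods and Data Analysis then fixes the test: "The self-reported sunscreen usage data will be dichotomized and analyzed by Chi-squared statistical test to establish whether sunscreen consumption will differ" between the arms. It adds "Two-sided *p*-values of <0.05 will be considered statistically significant" and calls for two-sided 95% confidence intervals.

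The Power Calculation uses two proportions, 25% and 50%, and arrives at 58 workers per group for 80% power, with 100 per group recruited. No site term, ICC, design effect or cluster method appears in the article.

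**The concern.** The comparison is between two sites and two other sites. Whatever makes one site's workers use more or less sunscreen than another's, apart from the intervention, enters the observed difference between arms. The chi-squared test takes its standard error from binomial variation among workers alone, so it has no term for variation between sites.

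This is the only test named for the study's main hypothesis. If sites differ, its 5% error rate is not held and its interval does not cover 95% of the time. A significant result could then reflect ordinary site-to-site variation and be read as an effect of dispensers and feedback.

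**Working it through.** **Inputs from the article.** Control 25%, intervention 50%, two-sided alpha 0.05, power 80%, 58 per group needed, 100 per group recruited, two sites per arm. I read "group" in the Power Calculation as arm, since 2 × 100 = 200.

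**Assumptions.** Sites of equal size, so m = 58/2 = 29 or m = 100/2 = 50 workers per site. The article gives no ICC, so a range is used.

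**1. The plan's own figure.** With p̄ = (0.25 + 0.50)/2 = 0.375,

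n = [1.96·√(2·0.375·0.625) + 0.842·√(0.25·0.75 + 0.50·0.50)]² / 0.25² = 57.7, so 58.

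This matches the stated 58. It is the formula for independently sampled workers (design effect 1), so clustering is absent from the sample size as well as from the test.

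**2. Design effect.** DE = 1 + (m − 1)·ICC. At m = 50 and ICC 0.02, DE = 1 + 49·0.02 = 1.98.

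**3. True error rate of the planned test.** Approximately 2·[1 − Φ(1.96/√DE)]. At m = 50 and ICC 0.02: 1.96/√1.98 = 1.393, giving 0.164. A beta-binomial simulation (200,000 replicates, 25% in every site, two sites per arm) gives 0.165. For ICC 0.005 the table shows the formula's result; the other rows are simulated.

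| ICC | DE, m = 29 | Type I error, m = 29 | DE, m = 50 | Type I error, m = 50 |
|---|---|---|---|---|
| 0 | 1.00 | 0.052 | 1.00 | 0.049 |
| 0.005 | 1.14 | 0.066 | 1.25 | 0.079 |
| 0.01 | 1.28 | 0.086 | 1.49 | 0.110 |
| 0.02 | 1.56 | 0.122 | 1.98 | 0.165 |
| 0.05 | 2.40 | 0.213 | 3.45 | 0.297 |

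**4. Confidence interval.** At 25% versus 50% with 100 per arm, the worker-level half-width is 1.96·√[(0.1875 + 0.25)/100] = 0.130. Multiplying by √DE gives 0.158, 0.182 and 0.241 at ICC 0.01, 0.02 and 0.05. Simulated coverage of the nominal 95% interval at these ICCs is 0.89, 0.83 and 0.70. Four sites in two arms leave 2·(2 − 1) = 2 degrees of freedom, with critical value 4.30 instead of 1.96, so the half-widths become 0.347, 0.400 and 0.529.

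**5. What a valid test can deliver.** An unadjusted site-level t-test on 2 df keeps its simulated error at 0.048-0.051 over these ICCs. Its power for 25% versus 50% is:

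| ICC | m = 29 | m = 50 |
|---|---|---|
| 0 | 0.37 | 0.53 |
| 0.01 | 0.31 | 0.41 |
| 0.02 | 0.27 | 0.34 |
| 0.05 | 0.21 | 0.24 |

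**The case against.** **The inflation is conditional.** It requires a positive ICC, and the article gives none. At ICC 0 the planned test is valid, and at ICC 0.001-0.005 the error is only about 0.055-0.079. This stands: a reader might infer that the p-value is certainly and badly wrong, and the article does not support that. It does make zero correlation implausible. Dispensers and posters are shared, the Discussion expects group monitoring to work because group members stimulate one another, and the Process Outcomes list colleagues' negative remarks as a barrier to use.

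**The sites are matched.** Matching on tasks, location and time-frame may well lower between-site variance. The chi-squared test, however, neither uses the matching nor estimates the variance that remains. Nor can a reader take the four sites as two defined pairs: the article matches control groups to intervention groups and names no one-to-one partners.

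**A detailed analysis plan is promised.** It may add much, but the article already names the primary test and its threshold. A later plan that respected site would have to replace that text.

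**The article does not say that p<0.05 proves effectiveness.** That is correct. It says that the test is to show whether use differs, and that the study is intended to provide evidence. The fault lies in the test's validity, not in a claim of proof.

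**Conclusion.** The primary analysis as written does not match the unit of assignment and needs to change before data are analysed. The direction is firm for any positive ICC; the size is not, because it rests on assumed ICCs and equal sites. Over ICC 0.005-0.05 and 29 to 50 workers per site, the nominal 5% error becomes roughly 7% to 30%, and the interval is too narrow by a factor of √1.14 = 1.07 to √3.45 = 1.86, before allowing for 2 degrees of freedom.

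A reader might also infer that a cluster-adjusted analysis would make the comparison confirmatory. It would not. Even with no between-site variation, the unadjusted site-level test has power of at most about 0.53 for the planned effect. It also corrects the variance only. Differences between sites that were not randomized can still bias the estimate; the Discussion acknowledges the lack of randomization, but not clustering.

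**What to change.** In Statistical Methods and Data Analysis:

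- Make the primary estimate a comparison of the four site-level results, two against two, with a t-interval on 2 df. Adjust for baseline sunscreen use, for example through a worker-level model without an arm term whose results are then averaged by site.
- Report all four sites individually. Use pairs only if one-to-one pairs are defined in advance. A paired analysis would leave 1 df (critical value 12.7), so pairing is better used for display.
- Label the worker-level chi-squared result descriptive.
- State that the 80% power in the Power Calculation does not apply to this analysis, give the site-level power with its ICC assumptions, and present the effectiveness comparison as exploratory.
- Keep confounding from site assignment as a separate limitation, and add clustering beside it.

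The change needs no extra sites or workers, only new wording and modest analysis work; recruitment had not started when the article was submitted. The real cost is the much wider interval and the low power shown above. Baseline adjustment may recover some of that power, but how much cannot be computed from the article. Confirmatory inference would need more sites.

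### The primary test collapses a five-level answer and ignores the baseline answer in a non-randomized study; an ordinal, baseline-adjusted analysis would use data already collected

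*Protocol article*

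**What the plan says.** All references are to the Protocol article.

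- *Primary Outcome*: the questionnaire asks how often sunscreen was applied daily over the last month, with the answers "never, seldom, sometimes, often, always". The contrast is then given as "Difference in the frequency of sunscreen use between the intervention and control groups will serve as the primary outcome".
- *Statistical Methods and Data Analysis*: "The self-reported sunscreen usage data will be dichotomized", and the groups are then compared by a chi-squared test. No covariate is mentioned for this comparison, and the categories that count as use are not named. The same section says "Two-sided *p*-values of <0.05 will be considered statistically significant" and closes with "Before data analysis, a detailed data analysis plan will be available".
- *Power Calculation*: the control rate comes from a Canadian study in which "25% of the outdoor workers used sunscreen regularly". The intervention rate is set at 50%, giving 58 per group for 80% power and 100 per group to be recruited.
- *Abstract*: the effect is to be assessed from questionnaires at baseline and after 12 weeks.
- *Design and Setting* and *Blinding*: four sites are assigned without randomization, and neither participants nor investigators are blinded.

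**The concern.** Two kinds of information are collected and then not used by the stated primary test.

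**The ordering.** With two categories, any movement inside one half disappears. A worker who goes from never to sometimes counts as unchanged at an often/always cut, yet this is a plausible effect of free, accessible sunscreen.

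**The baseline answer.** A chi-squared test on T=12 attributes to the intervention any difference in use that the sites already had at T=0. Matching on worksite, job task, location and time-frame does not match on sunscreen use. The T=0 answer is the most direct available control for this.

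A lesser matter is that the 25% and 50% behind the sample size are not tied to particular answers. Five ordered levels allow four cuts, and power differs considerably between them. At stake are the precision of the primary comparison and its protection against pre-existing differences between sites.

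**Working it through.** **Step 1: reproduce the stated sample size.** Inputs from *Power Calculation*: 25% and 50%, 80% power, two-sided 0.05. With pooled variance and no continuity correction, and a mean proportion of 0.375:

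n = [1.960·√(2·0.375·0.625) + 0.842·√(0.25·0.75 + 0.50·0.50)]² / 0.25² = (1.342 + 0.557)² / 0.0625 ≈ 57.7, so 58 per group.

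Power is 0.802 at 58 and 0.960 at 100. The article's figure is correct for a binary endpoint with independent workers.

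**Step 2: express the effect on the ordinal scale.** The odds ratio is (0.50/0.50)/(0.25/0.75) = 3. The article gives no distribution over the five answers, so one is assumed for controls: 30/25/20/15/10%, which puts 25% at often/always. Applying an odds ratio of 3 at every cut gives 12.5/16.4/21.1/25/25% in the intervention group, which is 50% at often/always.

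**Step 3: ordinal sample size (Whitehead).** The mean category proportions are 0.2125, 0.207, 0.205, 0.200 and 0.175, and their cubes sum to 0.0405.

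Total N = 12·(1.960 + 0.842)² / [(ln 3)²·(1 − 0.0405)] = 94.2 / (1.207·0.9595) ≈ 81.3, or about 41 per group.

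Across four assumed control distributions, all with 25% at often/always, the result is 41 to 43 per group.

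**Step 4: power by simulation.** Independent workers and a common odds ratio of 3 are assumed. Each figure is the range over the four control distributions, and the ordinal analysis is represented by a rank-sum test.

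| Analysis | 58 per group | 100 per group |
|---|---|---|
| Never vs rest | 0.50–0.82 | 0.73–0.97 |
| Never/seldom vs rest | 0.78–0.83 | 0.95–0.97 |
| Often/always vs rest | 0.80 | 0.96 |
| Always vs rest | 0.59–0.64 | 0.81–0.86 |
| Ordinal | 0.90–0.91 | 0.99 |

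**Step 5: drop the proportional-odds assumption.** Keep the control distribution of Step 2 and set the intervention answers to 30/15/5/35/15%. Often/always still rises from 25% to 50%, but never-users do not move. The odds ratios at the four cuts are then 1.0, 1.5, 3.0 and 1.6. Power is about 0.29 (ordinal) against 0.80 (binary) at 58 per group, and 0.45 against 0.96 at 100.

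**Step 6: what a post-hoc cut would cost.** With no effect, the chance that at least one of the four cuts gives p<0.05 is 14–17% two-sided (about 16% for the Step 2 distribution), or 7–8% in favour of the intervention against a nominal 2.5%. Four independent tests would give 1 − 0.95⁴ = 18.5%. These figures apply only if the arms are compared at all four cuts before one is chosen.

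**Step 7: baseline adjustment.** The documents give neither the expected T=0 difference between sites nor the correlation between the T=0 and T=12 answers, so its size cannot be computed. The case for it rests on the design: allocation is not randomized and the T=0 answer is already collected.

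**The case against.** **The cut belongs to the analysis plan.** The article condenses a fuller protocol and promises a detailed plan before analysis. This stands: the missing cut alone would be omitted detail and no error. The wording in *Power Calculation* also leans towards regular use, so the four cuts are not equally plausible.

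**A result-driven cut.** A reader might infer that the cut will be chosen once results are known and that the real error rate is therefore 16%. The article does not support this. It places the plan before analysis, and *Study Status* says recruitment had not started. The timing leaves room for a plan written after unblinded questionnaires are in, but does not say that this will happen.

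**The power gap is small at the planned size.** This also stands. At 100 per group it is about 3 points at the often/always cut. The gap of about 11 points belongs to 58 per group, the number needed before the allowance for drop-out.

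**The ordinal gain is assumed.** Step 5 shows it can reverse sharply. The *Introduction* reports resistance based on beliefs about tanning and masculinity, so never-users who do not move are conceivable. The ordinal model is therefore not better in every case.

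**A binary test with a matching sample size is coherent.** True, but this does not answer the unused T=0 response. The chi-squared test is the stated method, and in a non-randomized comparison it leaves out a covariate that the study already holds.

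**Conclusion.** The point holds as an improvement to a stated method. The primary analysis discards ordinal information and ignores the baseline response in a non-randomized study. Under a common odds ratio of 3 and an assumed control distribution, the ordinal analysis has power of about 0.91 against 0.80 at 58 per group and 0.99 against 0.96 at 100. All figures treat workers as independent; with two sites per arm, real power is lower for either analysis, and that is a separate matter.

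The documents do not support reading this as a sample-size error, since 58 is reproduced. Nor do they support an actual type I error of 16%, or a claim that the ordinal model wins whatever the shape of the effect. The firmest parts are adjustment for T=0 use and fixing the cut before enrolment, because neither depends on proportional odds.

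**What to change.** 1. Make the primary analysis a proportional-odds model of the five-level T=12 answer, adjusted for the T=0 answer, and report the common odds ratio with its 95% confidence interval.
2. State one cut before enrolment, often/always against the rest, and say that the 25% and 50% in *Power Calculation* refer to it.
3. Report the percentages at that cut by group, with a baseline-adjusted binary analysis, as supporting results.
4. If the sponsor keeps the binary endpoint as primary because a non-proportional effect is expected, fix the same cut and replace the unadjusted chi-squared test with, for example, logistic regression adjusted for T=0 use.

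**Cost.** Analysis wording only: no extra data, visits or participants. An odds ratio is less direct to read than a difference in percentages, which is why the percentages stay alongside. The ordinal model can also lose substantial power if the effect is not a proportional shift, so the choice between items 1 and 4 should be made and justified before enrolment.
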